#### Inflammatory markers

Blood IL-4, IL-5, IL-10, IL-13, PCR, and TNFα will be assessed [35]. The plasma will be centrifuged for 10 minutes at 3,000 rpm in a centrifuge refrigerated at 0 to 4 °C (Eppendorf, 5804-R), and the supernatant will be frozen in a freezer at −80°C for dosing. Dosing of cytokines and TNFα will be performed in plasma, in microplates (96 wells) sensitized with the antibody to the protein of interest, adhered to the wall of the plate wells by an immunoadsorbent substrate. The following human-specific kits will be used: human TNFα ELISA kit, human IL-4, IL-5 ELISA kit, human IL-10, *and* human IL-13 ELISA kit.

### Protocol

The assessments will be conducted in three visits, as described below (Fig. 1).

**Fig 1 Fig1:**
[figure not shown]
Flow of patients through the study

Visit 1: quality of life questionnaire, asthma control questionnaire, pre- and post-bronchodilator spirometry (400 μcg salbutamol), inflammatory assessment (blood collection), and cardiopulmonary exercise test on a cycle ergometer.

Visit 2: Assessment of strength and endurance of the quadriceps femoris and biceps brachii muscles with surface electromyography.

Visit 3: ISWT and an accelerometer will be used to assess physical activity in daily life.

The volunteers will be randomized to receive a pulmonary rehabilitation program (intervention group) or chest physiotherapy plus stretching exercises (control group), as described below by the website randomization.com.

### Intervention group

The intervention group will have a supervised rehabilitation program held twice a week. Each session will be 60 minutes in duration, with a minimum interval of 24 hours, for a period of 8 weeks. Each session will consist of three parts: aerobic training, strength muscle training, and chest physiotherapy. The aerobic training will be held for 35 minutes (10 minutes of warm up, 20 minutes on target load, and 5 minutes of cooling down) with an initial intensity of 60 % of the maximum load obtained in the maximal cardiopulmonary exercise testing or in the ISWT. The intensity will be gradually increased up to 80 %, so that fatigue or dyspnea values are kept between 4 and 6, according to the modified Borg scale [31]. When necessary, supplemental oxygen will be supplied during training to keep oxygen saturation greater than 92 %. Strength muscle training will be applied to the quadriceps femoris, biceps brachii, and deltoid muscles for 15 minutes. The intensity will be 40 to 70 % of maximal repetition (1 MR) in three sets of eight repetitions. Finally, for chest physiotherapy, the oral high-frequency oscillation device (Flutter®) will be used for 5 minutes. The volunteers in this group will receive a 200-μcg bronchodilator before starting the session each day.

### Control group

The control group will have chest physiotherapy and stretching exercises twice a week. Each session will be 60 minutes, with a minimum interval of 24 hours, for a period of 8 weeks. For each session, the oral high-frequency oscillation device (Flutter®) will be used for 10 minutes, 5 minutes in each lateral decubitus position, followed by stretching of the upper and lower limbs for 40 minutes. All exercises will be active, performed in sitting and lying positions without increasing the heart rate. The remaining 10 minutes will be used to discuss doubts about the disease and the use of the booklet.

Both groups will be oriented about the disease (proper use of medication, use of peak flow, triggering factors for crisis). On the date of the initial evaluation, they will take home a booklet with the main information about the given guidelines. All volunteers will be reevaluated after 8 weeks, when the same initial assessments will be performed again.

### Statistical analysis

The sample size was based on the run shuttle walk test levels and on the maximum load achieved in CPET [14]. Considering the stages of the shuttle, and assuming an alpha risk of 5 % and beta risk of 80 %, standard deviation of 1.6, and a difference in magnitude of 2.0 levels before and after the pulmonary rehabilitation program [14], the sample size needed was 27 patients in each group. Considering the load (W) achieved in the cardiopulmonary exercise testing, with a −3 ± 2 W difference pre- and post-intervention in the control group, and of 16 ± 7 [20] in the intervention group, with an alpha risk of 5 % and a beta risk of 95 %, the sample size needed was 10 patients in each group. Therefore, considering potential losses, 30 asthmatic patients will be recruited for each group, requiring a total of 66 volunteers.

The data normality will be analyzed using the Kolmogorov-Smirnov test. Parametric data will be represented as means (SD) and nonparametric data as medians (IQR (25th−75th percentiles ). Comparisons between groups and time (pre- and post-rehabilitation) will be analyzed by two-way analysis of variance (ANOVA), with the Bonferroni test post hoc, or by the Kruskal Wallis test, depending on the data adherence or non-adherence to the Gaussian curve. Correlation between variables will be analyzed by Pearson or Spearman correlation according to the data distribution. Three-way repeated measures ANOVA group vs endurance (0–100 % endurance time, 25 % increments time) vs time (pre- and post-) will be used to assess the dependency of the EMG variables and will followed by post hoc Student–Newman–Keuls pairwise comparisons, when appropriate. The value of *P* <0.05 will be set as significant. SPSS version 13 (Chicago, IL, USA) will be the statistical software used in the study.

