## Background

Asthma is one of the main chronic diseases in childhood. It is characterized by inflammation of the airways [1]. Individuals with chronic lung disease are more susceptible to present reduction in exercise tolerance, not only due to ventilatory constraints, but also due to systemic manifestations of pulmonary disease [2]. Thus, the more severe and the less controlled the disease, the higher the dyspnea and fatigue reported by patients. In general, the obstruction increases the airways resistance, hindering the physiological ventilatory response during physical exertion and leading to dyspnea [2]. This in turn leads to the patient having a more sedentary lifestyle, predisposing them to early fatigue and exercise intolerance.

Cardiopulmonary exercise testing (CPET) is the gold standard for determining exercise intolerance [3, 4]. As it is a high-cost assessment, few studies have used CPET as a method to evaluate asthmatic children and adolescents [5–9]. Villa and colleagues [6] described the reduction of oxygen uptake (VO_2peak_ ) in patients with moderate/severe asthma when compared to the control group. The same was observed by an English group that found VO_2max_ reduction in the asthmatic group [7, 8]. Those authors proposed that asthma severity could be an important factor in determining aerobic capacity. Some limitations were observed in those mentioned studies, such as not measuring asthma control (a factor that may influence the patient’s condition), the small number of assessed individuals, and not determining the corticosteroid dose used by patients with asthma.

Clinical field tests are a less expensive alternative to CPET in determining functional capacity. The incremental shuttle walking test (ISWT) is a simple and inexpensive test described by Singh and colleagues [10]. Several authors using ISWT assessment found a reduction in the functional capacity of adults with chronic lung disease and its association with lung function and quality of life [11–13]. To our knowledge, only Ahmaidi and colleagues [14] have used the run shuttle walk test in pediatric patients with asthma to determine their functional capacity by comparing with CPET.

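### The stated needs of 27 and 10 patients per group do not follow from their printed inputs, and power is mislabelled as beta risk; on those inputs the trial is larger than required, not underpowered

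*Protocol article*

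**What the plan says.** The Statistical analysis section gives two sample size calculations, one for each component of the primary outcome.

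- **Shuttle levels.** The calculation is introduced as "assuming an alpha risk of 5 % and beta risk of 80" per cent, with a "standard deviation of 1.6, and a difference in magnitude of 2.0 levels before and after the pulmonary rehabilitation program". The result is that "the sample size needed was 27 patients in each group".
- **Cycle ergometer load.** The pre-post change is −3 ± 2 W in controls and 16 ± 7 W in the intervention group. Alpha is 5% and beta risk is given as 95%. The result is that "the sample size needed was 10 patients in each group".

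The section then allows for losses without giving a rate, sets 30 patients per group, and gives a total of 66. It does not state sidedness, the test behind either calculation, or whether 1.6 is the SD of a single measurement or of the change. The planned analysis is a two-way ANOVA on group and time, or Kruskal-Wallis.

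The shuttle inputs cite the same reference as the study which, according to the Background, was the only one to "have used the run shuttle walk test in pediatric patients with asthma". The trial itself measures the ISWT.

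**The concern.** Three things look wrong in one paragraph. First, a difference of 2.0 with an SD of 1.6 is a standardised effect of 1.25, which should need far fewer than 27 per group at 80% power. The load effect is larger still, so 10 also looks too many. Second, beta is the probability of missing a true effect. A "beta risk of 80" per cent would mean 20% power, and 95% would mean 5%. Third, the 2.0 levels is described as a before-after difference, whereas the trial compares two randomised groups.

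These calculations are the only justification printed for the number of children enrolled. If the numbers do not follow from the inputs, a reader cannot tell whether the trial is comfortably sized or rests on an SD or difference that was not printed. Those two cases lead to different readings of a null result.

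**Working it through.** All inputs come from the Statistical analysis section. I read beta risk as power and alpha as two-sided 5%, and test the alternatives below.

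**1. Shuttle, with 1.6 as the SD of change**

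Normal approximation: n per group = 2 (z₀.₉₇₅ + z₀.₈₀)² SD² / d² = 2 × (1.960 + 0.842)² × 1.6² / 2.0² = 2 × 7.849 × 0.64 = 10.05, so 11. The exact noncentral-t calculation gives 12. Power at 27 per group is 0.9946.

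**2. Shuttle, with 1.6 as the SD of one measurement**

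SD of change = 1.6 × √(2(1 − ρ)), where ρ is the pre-post correlation, which is not given.

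- At ρ = 0.5 this equals 1.6, so step 1 applies.
- At ρ = 0 it is 1.6 × √2 = 2.26. The normal formula gives 2 × 7.849 × (2.26/2.0)² ≈ 20.1, so 21; noncentral t gives 22. Power at 27 per group is 0.890.

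**3. Can any standard reading give 27?**

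| Reading (d = 2.0) | n per group, normal / t |
|---|---|
| SD 1.6, 80%, two-sided | 11 / 12 |
| SD 1.6, 80%, one-sided | 8 / 9 |
| SD 1.6, 80%, paired, two-sided | – / 8 |
| SD 1.6, literal 20% power, two-sided | 2 / 3 |
| SD 2.26, 80%, two-sided | 21 / 22 |
| SD 2.26, 90%, two-sided | 27 / 28 |
| SD 1.6, 99.5%, two-sided | 27 / 28 |

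At alpha 5%, 27 appears only at powers that the article does not state. To need 27 at 80% power, the SD of change would have to be about 2.57 for a difference of 2.0, or the difference about 1.24 at SD 1.6 (2.62 and 1.22 by the normal formula).

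**4. Load**

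Difference = 16 − (−3) = 19 W. Pooled SD = √((2² + 7²)/2) = √26.5 = 5.15.

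Normal approximation at 95% power: 2 × (1.960 + 1.645)² × 26.5 / 19² = 1.9, so 2, which is too few for the approximation to be trusted. Noncentral t gives power 0.914 at n = 3 and 0.990 at n = 4, so 4 per group.

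The two SDs are very unequal, so power was also simulated with SDs of 2 and 7:

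| n per group | Pooled t | Welch t |
|---|---|---|
| 3 | 0.897 | 0.719 |
| 4 | 0.983 | 0.938 |
| 5 | 0.998 | 0.992 |
| 10 | 1.000 | 1.000 |

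The need is therefore 4 with a pooled test and 5 with Welch. Taking SD 7 in both arms gives 5 (t-test), and even there power at 10 per group exceeds 99.9%. At 95% power, figures of 8 to 10 arise if the minus sign is lost (16 − 3 = 13 W) and the SD is taken as 7 or √53 = 7.28. That does not follow from the printed inputs.

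**5. What 27 evaluable per group can detect at 80% power**

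- SD of change 1.6: 1.24 levels.
- SD of change 2.26: 1.24 × √2 ≈ 1.76 levels.

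**6. Recruitment**

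30 × 2 = 60, not 66; a total of 66 would be 33 per group.

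**The case against.** The strongest reply is that the article never says which SD it means. A reader might infer that 27 should simply be 12 and that true power is 99.5%. That holds only if 1.6 is the SD of change. If it is a single-measurement SD with no pre-post correlation, the need is 22 and power at 27 is 89%, so the gap is 5 per group rather than 15. This objection stands and is why both ends are shown. It does not rescue 27, which at 80% power and alpha 5% appears under none of the readings tried.

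It can also be said that the planned analysis is ANOVA, not a t-test. With time as a within-patient factor, the group-by-time test in a two-group, two-visit ANOVA is equivalent to a pooled two-sample t-test on change, so the benchmark is fair. But the article does not say how either sample size was computed. Replacing 10 by a flat 4 would swap one undocumented choice for another, since Welch needs 5.

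A reader might infer that wrong power figures mean an underpowered trial. The documents point the other way: both printed sizes exceed what their inputs need, and recruitment is driven by 27, so the error in 10 changes nothing. Likewise, beta risks of 80% and 95% are a slip whose intended meaning is plain, not a plan for 20% and 5% power.

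Finally, a reader might infer that 2.0 levels cannot be a between-group difference. The article describes it only as a before-after difference; the cited study is not at hand, and whether it had a comparison arm is not stated. What stands is that the article does not make the link to a between-group difference on the ISWT.

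**Conclusion.** The concern holds as an error of arithmetic and reporting. Neither 27 nor 10 per group follows from the inputs printed beside it, and power is labelled as beta risk in both calculations (beta would be 20% and 5%).

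For the shuttle, the inputs call for 12 per group if 1.6 is the SD of change, and up to 22 if it is a single-measurement SD with non-negative pre-post correlation. Stated power is 80% against about 99.5% or 89% at the two ends. For load, the need is 4 or 5 depending on the test, and 10 per group gives more than 99.9%, not 95%. These figures assume two-sided 5%, normally distributed changes, equal allocation, and a between-group comparison of change.

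The consequence is a justification that is wrong and cannot be traced, not a demonstrated loss of power. The true inputs may differ from those printed. If so, the detectable effect is unknown to the reader until they are disclosed.

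**What to change.** Rewrite the sample size paragraph:

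1. State the inputs actually used to obtain 27 and 10: the SD and whether it is of the change, the difference as a between-group difference in change, the test, and the sidedness.
2. If the printed inputs are the true ones, correct the results. For the shuttle: 12 per group (SD of change 1.6) or 22 (SD of change 2.26), with about 99.5% or 89% power at 27. For load: 4 (pooled t) or 5 (Welch), with more than 99.9% power at 10.
3. Replace beta risk by power, at 80% and 95%.
4. State what 27 evaluable patients per group can detect at 80% power: 1.24 levels if the SD of change is 1.6, about 1.76 if it is 2.26.
5. Say that the 2.0 levels and the SD come from a before-after result on a run shuttle test, and why they are taken to apply to a between-group comparison on the ISWT.
6. Reconcile 30 per group (60) with the total of 66, and give the assumed loss rate.

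The cost is one paragraph. Recruitment need not change on account of the power calculation, but which of the two recruitment totals applies has to be settled.

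### The recruitment target does not add up: 30 children in each of two groups is 60, but the same sentence asks for 66, and nothing stated explains the other 6

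*Protocol article*

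**What the plan says.** The Statistical analysis section makes two calculations. For the shuttle test, "the sample size needed was 27 patients in each group". For the load reached in the cardiopulmonary exercise test, "the sample size needed was 10 patients in each group". It then combines them and adds an allowance: "30 asthmatic patients will be recruited for each group, requiring a total of 66 volunteers".

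The number of groups is not in doubt. The Protocol section, under the list of visits, says "The volunteers will be randomized to receive a pulmonary rehabilitation program (intervention group) or chest physiotherapy plus stretching exercises (control group"). The abstract and the Intervention group and Control group sections describe the same two arms and no others.

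**The concern.** The per-group figure and the total stand in one sentence and cannot both be right for two groups of equal size. The sentence is intact, so the mismatch does not come from redaction or text extraction. An article may well leave detail to a fuller protocol, but here both numbers are printed and they disagree.

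Two things are left open. One is how many children are to be randomised, in a trial that the Trial status section describes as already recruiting. The other is how much loss the plan allows for. The second matters because losses are built into the design: the Study design section removes children who do not complete the evaluations, who interrupt care or drug treatment, or who miss more than 20% of sessions.

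**Working it through.** **Inputs, all from the protocol article**

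- Groups: 2 (abstract; Protocol, Intervention group and Control group sections).
- Recruited per group, after allowing for losses: 30 ("considering potential losses, 30 asthmatic patients will be recruited for each group").
- Total: 66 ("requiring a total of 66 volunteers").
- Calculated size per group: 27 (shuttle) and 10 (exercise-test load). The larger, 27, governs.
- Loss rate: none stated.
- Allocation: equal, implied by one number for each group.

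**Reproducing the total**

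Total = groups × number per group = 2 × 30 = 60. The stated total is 66. The gap is 6, and 6/60 = 10%. Working back from the total, 66/2 = 33 per group.

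**What each number implies about losses**

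With recruited = needed / (1 − loss), loss = 1 − needed/recruited:

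- 27 to 30 per group: 1 − 27/30 = 10.0%.
- 27 to 33 per group: 1 − 27/33 = 18.2%.

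**Possible routes to 66**

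- A single allowance of about 18% on the calculated 54: 54/(1 − 0.18) ≈ 66. This means 33 recruited per group, which contradicts 30.
- A second allowance on top of 60: 60 × 1.10 = 66, or equivalently 1 − 60/66 = 9.1% lost. If those 6 are lost after randomisation, 33 per group are randomised, which again contradicts 30. If they are lost before randomisation, 66 enrolled would give 60 randomised and the two figures could stand together. The article does not say so.

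**Is the stated size at risk?**

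The calculated requirement is 2 × 27 = 54. Both 60 and 66 exceed it before losses.

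After losses the answer depends on a rate that the article does not give. As an illustration only, I **assume** 10%, 15% or 20% loss, independent between children. The binomial probability of keeping at least 27 is:

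| Recruited per group | Assumed loss 10% | 15% | 20% |
|---|---|---|---|
| 30, one group | 65% | 32% | 12% |
| 33, one group | 96% | 78% | 50% |
| 30, both groups | 42% | 10% | 2% |
| 33, both groups | 92% | 61% | 25% |

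The rows for both groups are the squares of the one-group probabilities (for example 0.647² = 0.42).

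These are chances of reaching the plan's own 27. They are not power. On the article's shuttle inputs (difference 2.0 levels, SD 1.6, two-sided 5%, and 80% read as power), an ordinary two-group comparison needs 2 × (1.96 + 0.84)² × 1.6² / 2.0² ≈ 10.05, rounded up to 11 per group. With 24 per group, which is 20% lost from 30, power is about 99%. It is about 85% if the SD of change is taken as 1.6 × √2.

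**The case against.** The strongest reply is that 66 counts children who enter assessment, not children randomised. The abstract places three assessment visits before randomisation, the Study design section excludes those who do not complete the evaluations, and 60 × 1.10 is exactly 66. The phrase about potential losses could also govern the whole sentence, including the 66. This reading is plausible and any correction has to allow for it. It does not clear the sentence, because the article states neither a screening allowance nor a split between enrolled and randomised, and it describes the 30 per group as recruited.

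It can also be said that the matter is small. Both totals are above 54, and neither an outcome nor a test depends on which is right. That holds too, and it limits the point to an undefined target.

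A reader might go further and infer that the trial is likely to be underpowered, quoting the 12% or 2% in the table. The documents do not support this. The loss rates are assumed, and 27 is not a threshold below which power collapses on the article's own inputs.

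A reader might also infer that the ambiguity lets an open-label trial stop at whichever total suits the results. The article does not call the trial open-label and describes no interim look at outcomes, so this would be speculation. Nor does it give a length for the randomisation list, so no error there can be claimed.

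**Conclusion.** The sample size sentence contradicts itself: 2 × 30 = 60, not 66, and nothing stated reconciles the two. The gap is 6 children, 10% of 60. This conclusion rests only on there being two equal groups, which the article makes clear. It does not depend on any assumed loss rate.

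The article does not show which of the two figures was intended. The implied allowances of 10% and 18% are back-calculated, not planned. The discrepancy does not by itself threaten the stated size before losses. That 27 does not follow from its own inputs as a two-group comparison is a separate matter and does not affect this one.

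**What to change.** Replace the sentence with one consistent target that states:

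- the number randomised per group and in total;
- whether 66 includes children lost before randomisation;
- the loss rate actually assumed, and whether it applies before or after randomisation.

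Three versions would be consistent: 30 per group and 60 in total; 33 per group and 66 in total; or 66 enrolled in order to randomise 60, 30 per group. The authors should choose the one that was planned. They should not adopt 10% or 18% as a rationale merely because it fits the arithmetic. If retention probabilities are quoted in support, the loss rates behind them should be labelled as assumptions.

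The cost is one sentence. The approved and registered sample sizes are not given in the article, so the authors should check the corrected figure against those records.

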## Methods

### Study design

This is a randomized clinical trial to be conducted in the pulmonary rehabilitation laboratory at University Nove de Julho. Clinically diagnosed asthmatic patients will be recruited in the Allergy, Clinical Immunology and Rheumatology Clinic at the Department of Pediatrics of Sao Paulo School of Medicine, Federal University of Sao Paulo. The individuals will be enrolled in the study after their legal guardians have read, agreed to, and signed the informed consent form. The current project was approved by the Associacao Educacional Nove de Julho Ethical Committee, Sao Paulo, Brazil, number 738192/2014.

The study will include patients diagnosed with asthma, between 6 and 18 years old, who are under medical treatment and disease control according to the Global Initiative for Asthma (GINA) criteria [1]. Those who fail to carry out the protocol evaluations, who interrupt medical care and/or drug-based treatment, who present with acute lung infection, other chronic lung diseases, or other comorbidities (neuropathies, heart disease), and those who miss more than 20 % of the rehabilitation sessions will be excluded from the study.

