### Outcomes

The primary outcome will be the physical capacity assessed by the cardiopulmonary exercise testing and ISWT. The secondary outcomes will be quality of life, peripheral muscle strength, and inflammatory markers.

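### The group-by-time ANOVA planned for both primary measures names no efficacy contrast and does not adjust for baseline, and its Kruskal-Wallis fallback cannot test a difference in change

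*Protocol article*

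**What the plan says.** The protocol article, Outcomes, sets the endpoint: "The primary outcome will be the physical capacity assessed by the cardiopulmonary exercise testing and ISWT". The Statistical analysis section gives one method for it and for the other non-EMG outcomes: "Comparisons between groups and time (pre- and post-rehabilitation) will be analyzed by two-way analysis of variance (ANOVA), with the Bonferroni test post hoc". A normality check decides whether a rank test takes its place: "or by the Kruskal Wallis test, depending on the data adherence or non-adherence to the Gaussian curve".

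The same paragraph describes the EMG model as "Three-way repeated measures ANOVA group vs endurance", crossed with pre/post time. That is the only model called repeated measures. No covariate is named for any model, and no term or contrast is named as the test of the treatment effect.

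The shuttle sample size assumes "standard deviation of 1.6, and a difference in magnitude of 2.0 levels before and after the pulmonary rehabilitation program". The end of the Control group section has every participant repeat the initial assessments after 8 weeks, so a baseline value of each outcome will exist.

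**The concern.** The trial asks whether training changes physical capacity more than chest physiotherapy with stretching does. Only a between-group contrast of change, or of the 8-week value given baseline, answers that.

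A two-way ANOVA yields a group main effect, a time main effect and an interaction, and only the interaction bears on the question. Each factor has two levels, so a post hoc test adds nothing to a main effect. The Bonferroni step can only compare the four group-by-time cells, and the pre-post comparison within each arm is among them.

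Three things are at stake:

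- Whether each child's two values are treated as paired. If not, the variation between children in a sample aged "between 6 and 18 years old" goes into the error term.
- Whether a result of 'significant in training, not in control' could be reported as an effect.
- Whether non-normal data receive a test that can address the question at all.

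**Working it through.** **Inputs.** SD 1.6 levels, planned effect 2.0 levels and 27 per group come from the Statistical analysis section, as does the target of 30 per group. Assumed here: two-sided 5% tests, SD 1.6 as the between-child SD at each visit, and a pre-post correlation ρ of 0.5 to 0.8. The document gives no ρ.

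**The plan's own figure.** With "assuming an alpha risk of 5 % and beta risk of 80" % read as 80% power, n = 2(1.960+0.842)² × 1.6²/2.0² = 10.05, so 11 per group. The protocol says "the sample size needed was 27 patients in each group". The figure does not reproduce from the stated inputs. That is a separate matter, and 27 and 30 per arm are taken below as given.

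**Variance of the estimated effect, n per arm, SD σ.**

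- Repeated-measures interaction (equal to comparing changes): 4σ²(1−ρ)/n
- ANCOVA on baseline: 2σ²(1−ρ²)/n
- Ratio ANCOVA/interaction: (1+ρ)/2, which is 0.75 at ρ = 0.5, 0.85 at 0.7 and 0.90 at 0.8

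The interaction test therefore needs 33%, 18% and 11% more patients than ANCOVA for the same precision (1/0.75, 1/0.85, 1/0.90).

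**Literal factorial fit, pre and post treated as independent.**

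- Interaction: the model uses variance 4σ²/n where the truth is 4σ²(1−ρ)/n. Its standard error is too large by 1/√(1−ρ), which is 1.41 at ρ = 0.5 and 2.24 at 0.8. True type I error is 2[1−Φ(1.96/√(1−ρ))], about 0.6% at ρ = 0.5 and near zero at 0.8.
- Group main effect: the model uses σ²/n where the truth is σ²(1+ρ)/n. Type I error is 2[1−Φ(1.96/√(1+ρ))], which is 11.0% at ρ = 0.5 and 14.4% at 0.8. Simulation gives 11–15%.

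**Simulated power for the difference in change, 30 per arm.**

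| Effect | ρ | Factorial interaction | Repeated-measures interaction | ANCOVA |
|---|---|---|---|---|
| 0.8 levels (0.5 SD, assumed) | 0.5 | about 20% | 48–49% | 58–59% |
| 0.8 levels (0.5 SD, assumed) | 0.8 | about 10% | 85–86% | 88–89% |
| 2.0 levels (1.25 SD, planned) | 0.5 | about 98% | above 99% | above 99% |
| 2.0 levels (1.25 SD, planned) | 0.8 | above 99% | above 99% | above 99% |

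At 27 per arm and 2.0 levels the factorial form still has 96% power at ρ = 0.5 and above 99% at 0.8.

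**Within-arm tests with no group difference.** If each arm's pre-post test is significant with probability p, exactly one arm is significant with probability 2p(1−p). This peaks at 50% when p = 0.5. With an assumed common improvement of 0.4 levels, 27 per arm and a Bonferroni correction over the two within-arm tests, simulation gives 27% at ρ = 0.5 and 47% at ρ = 0.8. ANCOVA and the repeated-measures interaction hold 5% in the same data. With no common change, the figure is about 5%.

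**Kruskal-Wallis.** It compares independent groups in one dimension. Applied to group-by-time data, it uses neither the pairing within a child nor an interaction.

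**The case against.** The best defence is that the factorial fit is inferred from one missing label. The sentence compares pre and post values, the same assessments are repeated in the same children, and the EMG model with the same pre/post factor is called repeated measures. A condensed article may have dropped the qualifier. Fitted that way and judged on the interaction, the analysis is a valid between-group comparison of change, and preferring ANCOVA is a matter of efficiency. The named contrast and covariates could also sit in an analysis plan that is not shown. This largely stands: the document does not say that pre and post are treated as independent.

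Three stronger readings are tempting, and the document does not support them.

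- *Power collapses.* This needs the factorial fit and an effect well below the planned one. At 2.0 levels with SD 1.6 it does not happen.
- *The planned CPET load effect would be missed.* The protocol's changes differ by 16 − (−3) = 19 W. The factorial standard error at 30 per arm is SD × √(4/30) = 0.365 SD, so 19 W reaches the critical value of about 1.98 only if the between-child SD is below roughly 26 W. No such SD is given, so this can be neither shown nor excluded.
- *Half of null trials would mislead.* Fifty per cent is the maximum over p, and the protocol nowhere says that efficacy will be concluded from within-arm tests.

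The defence does not remove the point. The protocol states a method and does not merely leave one open. Post hoc cell comparisons are part of that method, and Kruskal-Wallis fails under any reading of the ANOVA.

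**Conclusion.** The concern holds in a limited form. The stated analysis of both primary measures omits the baseline covariate, leaves the efficacy contrast unnamed, and falls back on a test that cannot address a difference in change.

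Under the ordinary reading (repeated measures, judged on the interaction), the cost is efficiency only: 11% to 33% more patients than ANCOVA for ρ between 0.8 and 0.5. It is negligible for power at the planned shuttle effect. Under the literal factorial reading, the interaction test is very conservative and weak for small effects, and the group main effect rejects too often.

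Within-arm tests create a risk of misreading whose size depends on the common change over 8 weeks. These sizes rest on assumed values of ρ, of the smaller effect and of the common change.

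The change is worth making because it settles which analysis is meant and costs nothing in data.

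**What to change.** Make the primary analysis of each primary measure an ANCOVA of the 8-week value on randomised group with the baseline value as covariate. Report the adjusted between-group difference with its 95% CI. Age may be added as a covariate, but its gain is not quantified here.

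For non-normal data, replace Kruskal-Wallis with a baseline-adjusted rank-based analysis or a between-group comparison of changes.

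If ANOVA is kept, call it a mixed repeated-measures ANOVA and name the group-by-time interaction as the sole efficacy test. In either case, state that within-arm pre-post tests are descriptive.

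The cost is a few sentences in the Statistical analysis section. The baseline values and age are already available, and neither recruitment nor visits change.
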